###### 9.3 Adverse Events and Serious Adverse Events

***Serious Adverse Event (SAE):*** Any adverse event that:

- Results in death
- Is it threatening, or places the participant at immediate risk of death from the event as it occurred?
- Requires or prolongs hospitalisation.
- Causes persistent or significant disability or incapacity.

# 10. DATA COLLECTION TIME POINTS

| **Timepoint** | **Grouped Variables Collected (Indicative Examples)** | **T pi** | **NT** | **C** |
| --- | --- | --- | --- | --- |
| Recruitment | Demographics: Name, Age, Sex, MRN, Contact No.  Administrative: Fee status, Unit/Hospital Admission/Discharge dates and times  Clinical: Comorbidities, Admission source/type/reason, SARI  Tracheostomy-specific: Tracheostomy date & reason, Previous inclusion  Outcomes: Nature of disposal | ✔ | ✔ p | ✔ p |
| Post Enrollment | Vitals & Parameters: RR, HR, BP, Temp, GCS, AVPU, SpO2, PaO2, PaCO2, FiO2, Arterial pH  Labs: Hb, WBC, Platelets, Electrolytes (Na+, K+, HCO3-), Creatinine, Bilirubin, PCV, Urea  Support: CV support, Vasopressors, Sedation, Renal replacement  Treatment: Antimicrobial use & type  Functional: Clinical frailty, Patient status/location  Trache-specific: Seizures, Oxygen flow rate | ✔ | ✔p | ✔ |
| In ICU (Daily) | Daily Vitals: RR, HR, BP, Temp, GCS, SpO2, FiO2, PaO2  Support: CV support, Vasopressors, Sedation  Access: CVC, arterial line, urine catheter, HD catheter  Imaging & Labs: Lung radiology, Platelets, WBC (high/low), Creatinine, Bilirubin, PT  Treatment: Antimicrobials, Specimen collection/report  Safety: Pressure sores  Trache-specific: Oxygen flow, Seizures, Location | ✔ | ✔ p | ✔ |
| Post ICU (Up to Discharge) | RFSD Day Status: Patient/location status, date, timepoint  Socio-Demographics: Education, occupation, income, SES, eHealth/digital literacy (patient & caregiver)  CG Details: Name, age, gender, relation, contact, address  Clinical: Devices (PEG/NG/Jejunostomy, tracheostomy tube), vasopressors, renal replacement, stepped-down status  Outcome Monitoring: EQ5D, VAS, Health issues, Interventions | ✔ | ✘ | ✘ |
| During Training | Trainee Info: Name, age, gender, relationship, education, contact  Scores: Pre/post training scores (suction, feeding, bed care), Trainer observations  FAQs Topics: Tracheostomy, suctioning, feeding, hygiene, diet, catheter care, general questions | ✔ | ✘ | ✘ |
| Exit Training | Exit Training: Date, final training score | ✔ | ✘ | ✘ |
| Mobile App Distribution | Logistics: Days since RFSD, time taken  User Feedback: Issues, facilitators/barriers, app utility for training | ✔ | ✘ | ✘ |
| Equipment Delivery | Equipment Provided: Type, provider, training demo done  Logistics: Delay, placement guidance, agreement to T&C, ergonomics discussion  Barriers and facilitators | ✔ | ✘ | ✘ |
| Home Visit | Care Quality: Hygiene, equipment use, trache/RT/foley care, calorie tracking, mobilisation  Support: App usage, local HCC contact, medications | ✔ | ✘ | ✘ |
| At Discharge | Dates & Status: Unit/hospital discharge date & time, CPR, discharge note  Trache-Specific: Ongoing trach care, reason for early discharge, diet chart  CG Consistency: Same carer since enrollment, eHealth tools & scores  Outcome Measures: EQ5D, VAS, CBS score, Semi-structured interview | ✔ | ✔ p | ✔ |

Table 3. Data to be collected at different time points. Tpi-Tracheostomy (post-implementation), NT=Non-Tracheostomy, C= pre implementation patients with Tracheostomy) , p=partial

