| **Secondary**  **Outcome**  **Measures** | 1. Patient and Carer Reported Outcomes measured at 30 days. 2. Health-related QoL (EQ-5D-3L) of patients at hospital discharge and at 30 days 3. Carer Burden Scores of carers at hospital discharge and at 30-day post-discharge 4. Measures of safety   a) Hospital device-associated infections, e.g., CAUTI, VAP, HAP, in the rate of events within the group per unit time.  b) Clinical outcomes – Bed sores, Tracheostomy block, Clinical Deterioration, readmission, and mortality (rate/ unit time).   1. Measures of process 2. Adherence to the intervention  - % consented - % Trained for at least three sessions - Number of sessions missed. - Subjective and objective scores of carers' confidence post-training - % using the mHealth app at least once spontaneously after home discharge - % 1 week home visits completed - Data entry (completion)  1. Clinical 2. Measures for Direct Analysis 3. Resource use and expenditure questionnaire |

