**5.2.2 Secondary outcomes**

i. Patient and Carer Reported Outcomes measured at Day 30.

a. Health-related Quality of Life (QoL) with EuroQOL 3 dimensions (EQ-5D-3L) of patients at hospital discharge and at Day 30 after hospital discharge?

b. Carer Burden Scores (CBS) of carers at hospital discharge and at 30-day post-discharge

c. Alert, Verbal, Pain, Unresponsive (AVPU) scores at discharge and at 30-day

ii. Measures of safety

a. Hospital-acquired infections- central line-associated bloodstream infections, catheter-associated urinary tract infections, ventilator-associated pneumonia, surgical site infections, in the rate of events within groups per unit time.

b. Clinical outcomes – Length of stay in ICU, frequency of bed sores, tracheostomy blockage, Clinical Deterioration (as declared by the treating team in the hospital or deterioration in AVPU status at follow-up), readmission to ICU or hospital (after discharge and up to 30-day follow-up) and mortality at follow-up of 30 days (rate/ unit time).

iii. Measures of process (post-intervention stage)- Implementation Measures

1. Adherence to the intervention

- %Eligible patients approached
- % consented
- % Trained for at least 3 sessions
- Number of sessions missed.
- Subjective and objective scores of carers' confidence post-training
- % using the mHealth app at least once spontaneously after home discharge
- % 1 week home visits completed
- Data entry (completion)

| **Outcome** | **Definition** | **Assumed relationship** |
| --- | --- | --- |
| Time from the clinician's decision of readiness for step down | Time (days) from the Clinician declaring the patient ready for step down to discharge home under a carer or a paid caregiver.  *Home is defined as the usual residence, or family home, or a rental house in the vicinity of the hospital, but not another healthcare facility* | The intervention will reduce hospital length of stay/ bed days. |
| ICU/ HDU length of stay | Time from ICU admission to discharge to an intermediate facility (ie HDU/ ward) within the same hospital | The intervention will reduce ICU length of stay/ bed days. |
| Complications | Hospital-associated infections are defined as clinician-reported suspected/confirmed infection + new fever or new change in antibiotic. | There will be a reduction in HAI following the intervention. |

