###### *Table 2: Schedule of evaluations in the intervention group.*

**9.2 Description of Evaluations:** Detailed description in the manual of the intervention and evaluations

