**Amendment to Statistical Analysis Plan**

As per the initial protocol, the analysis plan proposed conducting either an **interrupted time series (ITS)** analysis or a **pre–post design**, contingent on the achieved sample size. However, following the withdrawal of Site C, it was decided that the **primary analysis** would be a **pre–post comparison** of outcomes with Sites A and B, assessing differences before and after intervention implementation. In addition, a **secondary interrupted time series analysis** would be conducted, incorporating data from Sites A, B, and D (AIIMS Bhubaneswar) to evaluate temporal trends across these three participating centres. This modification ensured analytical rigour and retained the study's capacity to assess both immediate and longitudinal impacts of the AIR intervention.

The process evaluation was amended to align the planned methods with how implementation unfolded in practice across sites. While the initial plan assumed a uniform, time-bounded process evaluation across participating centres, early fieldwork identified inter-site variation in organisational readiness, discharge norms, and stakeholder engagement that directly influenced intervention delivery. Accordingly, the process evaluation was refined to emphasise longitudinal, observation-led inquiry across pre-implementation, implementation, and maintenance phases; to expand the use of ethnographic data and iterative analysis; and to explicitly examine contextual determinants of adoption, adaptation, and non-implementation. Analytical methods were clarified to include inductive realist-informed thematic analysis with subsequent deductive application of the CFIR framework. These amendments ensure that the process evaluation accurately captures fidelity, adaptation, and contextual constraints affecting delivery and supports valid interpretation of effectiveness outcomes

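### Between ICU and discharge, Table 3 schedules event monitoring for AIR patients but not for baseline tracheostomy patients, so a whole-stay before-after comparison of bed sores and tracheostomy blockage is biased against AIR.

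*Combined protocol and SAP*

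**What the plan says.** Section 5.2.2 (ii.b) lists among the safety outcomes "frequency of bed sores, tracheostomy blockage, Clinical Deterioration", with no restriction to the ICU. The Study Summary (1.0) gives the scale: "Bed sores, Tracheostomy block, Clinical Deterioration, readmission, and mortality (rate/ unit time". In 5.2.2 only the implementation measures are tied to one phase ("Measures of process (post-intervention stage"); the safety measures are not. The Amendment to Statistical Analysis Plan in section 11 makes the primary analysis a pre-post comparison "of outcomes with Sites A and B, assessing differences before and after intervention implementation".

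Recording is set out in Table 3 (section 10), whose legend reads "C= pre implementation patients with Tracheostomy". Column C is therefore the before group.

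- In ICU (Daily) includes "Safety: Pressure sores". Ticked for T pi and C, partial for NT.
- Post ICU (Up to Discharge) includes "Outcome Monitoring: EQ5D, VAS, Health issues, Interventions". Ticked for T pi, crossed for C and NT. The RFSD date is in this same row.
- At Discharge includes the discharge note. Ticked for T pi and C, partial for NT.

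Tracheostomy blockage is named in no row. The schedule in 9.1, which lists adverse events, is captioned "Schedule of evaluations in the intervention group".

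**The concern.** A before-after comparison of event rates needs the same chance of recording an event in both phases. Here, once a patient leaves the ICU, the AIR period has a scheduled place to note health issues and interventions, and the baseline period does not. A ward bed sore or a blocked tube in a baseline patient reaches the data only if someone writes it into a less structured source.

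The control arm cannot repair this. Non-tracheostomised patients cannot have a blockage. For bed sores, Table 3 does not split the NT column by phase, so the change in recording falls on the tracheostomy patients alone and a controlled comparison would carry it through.

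AIR moves care of these patients to families, so bed sores and blocked tubes are events that clinicians will look at when judging its safety. Under-recording at baseline could produce a spurious harm signal or conceal a genuine reduction.

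**Working it through.** **The plan's own figure.** Weekly points (16 before, 16 after) and about 5 discharges per point come from 1.0 and 2.0: (16 + 16) × 5 = 160. This reproduces the stated 160 tracheostomy patients, or 80 per phase. If Sites A and B supply two thirds of them (assumed), the primary comparison has 160 × 2/3 ÷ 2 ≈ 53 per phase.

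**Recording bias.** Let f be the share of baseline events that arise after ICU, and c the share of those still captured at baseline by another route. Assume capture is complete under AIR and unrecorded baseline time is scored event-free. The documents give neither f nor c. Then

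recorded ratio (AIR / baseline) = true ratio ÷ [1 − f(1 − c)].

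| True ratio | c | f = 25% | f = 50% | f = 75% |
|---|---|---|---|---|
| 1.0 | 0 | 1/0.75 = 1.33 | 1/0.50 = 2.0 | 1/0.25 = 4.0 |
| 1.0 | 0.5 | 1/0.875 = 1.14 | 1/0.75 = 1.33 | 1/0.625 = 1.6 |
| 0.5 | 0 | 0.67 | 1.0 | 2.0 |
| 0.5 | 0.5 | 0.57 | 0.67 | 0.8 |

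With c = 1, meaning equal capture, the recorded ratio equals the true ratio. The formula fits bed sores best, because their ICU part is recorded daily in both phases. For blockage even the ICU part has no named field in either phase.

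**Chance of a false harm signal.** Treat the outcome as yes/no per patient, with a true risk of 20% in both phases and a two-sided 5% test (normal approximation). All of these are assumptions. The risk recorded at baseline is 0.20 × [1 − f(1 − c)].

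| f, c | Recorded risk, AIR vs baseline | Expected events, 80 per phase | False harm, 80 per phase | False harm, 53 per phase |
|---|---|---|---|---|
| 50%, 0 | 20% vs 10% | 16 vs 8 | 42% | 30% |
| 75%, 0 | 20% vs 5% | 16 vs 4 | 82.5% | 65% |
| 50%, 0.5 | 20% vs 15% | 16 vs 12 | 13% | 10% |

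With equal capture the chance in that direction is 2.5%.

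**The case against.** Several counter-arguments have force.

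- **Other sources exist.** The At Discharge row, with the discharge note, is ticked in full for C. Table 3 presents its variables as examples, and 9.2 defers detail to a manual that is not in the documents. The Post ICU row names neither outcome. So it cannot be said that baseline ward events have nowhere to be recorded. What stands is the difference: a cross against a whole row is not undone by calling its contents examples, and AIR patients have the discharge note as well as the monitoring row.
- **The caption in 9.1 is ambiguous.** Section 2.0 defines controls as non-tracheostomised patients from the same weeks as the intervention group, and the arm of 160 spans both phases, so the term can cover baseline tracheostomy patients. The training columns in 9.1 point the other way. The caption supports the point but does not prove it.
- **The cross may be a table error.** The same row holds the RFSD date, without which the primary outcome cannot be calculated for baseline patients, and 5.3.1 places recruitment at RFSD. If it is an error, Table 3 needs correcting. If not, the gap reaches the primary outcome too.
- **The comparison is inferred.** Section 11 says only outcomes, the assumed relationships in Table 2 of section 5.2 mention neither event, and 2.0 defers analysis to a later SAP. Against this, the lay summary (3.0) asks whether AIR reduces complications relative to patients without access to it.

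A reader might infer that AIR is bound to look harmful. The documents do not support that. It requires unrecorded baseline time to be scored as event-free, which they do not say, and the table above shows a true halving recorded as 1.0 or less in five of six settings.

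A reader might also reach large ratios by assuming a 14-day wait from RFSD to home with 2, 4 or 6 days in ICU and no other capture: 14/2 = 7.0, 14/4 = 3.5, 14/6 = 2.3. Those figures depend on cutting the window to RFSD-to-home, which 5.2.2 does not do. Adding an assumed 14 recorded ICU days before RFSD gives 28/16 = 1.75, 28/18 = 1.56 and 28/20 = 1.40. With only observed days in the denominator the ratio is 1.0.

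**Conclusion.** The concern holds as unequal recording. Followed as written, Table 3 gives AIR patients scheduled monitoring between ICU and discharge and gives baseline tracheostomy patients none, for two safety outcomes that are not confined to the ICU. The direction is against AIR. The size is not determined by the documents: with equal true risk it is 1.33 to 4.0 if no ward event is otherwise captured at baseline, and 1.14 to 1.6 if half are, for f between 25% and 75%. These figures assume complete capture under AIR and unrecorded baseline time counted as event-free. Bed sores arising in ICU are unaffected. If the cross is a table error and baseline patients were monitored in the same way, the bias disappears and only the table and the missing outcome definitions need attention.

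**What to change.** 1. Reconcile column C of the Post ICU row with 5.2.1 and 5.3.1, and state what was collected at baseline, including the RFSD date.
2. Define new pressure sore and tracheostomy blockage as events, and record each with its date from RFSD to discharge, from the same source (for example the nursing record), for both T pi and C.
3. State the denominator for each rate, and that time without observation is not counted as event-free.
4. If baseline post-ICU data were not collected and cannot be recovered, restrict the pre-post bed-sore comparison to ICU days, with ICU days as the denominator. Report AIR-period ward bed sores and blockage descriptively, without a comparator claim.

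The cost is two dated items, or a short restriction in the SAP. Section 11 describes baseline collection in the past tense, so retrospective extraction or item 4 may be the practical route. The downside of item 4 is a shorter comparable observation time and no before-after statement on blockage.

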# 11. AMENDMENTS TO INITIAL PLAN AND PROTOCOL WITHIN THE STUDY PERIOD

**11.1 Rationale**

During the implementation of the AIR intervention scale-up, several amendments were necessitated based on the concurrent process evaluation findings from the three selected centres. The initial plan involved implementing the family-supported home discharge model for chronically ill tracheostomised patients RFSD at three new centres after it had been discontinued at the pilot site, AIIMS Bhubaneswar, and conducting process evaluations at each site to assess feasibility, fidelity, and contextual adaptability.

**Description of Change**

Findings from the process evaluation revealed substantial inter-site variability in context and stakeholder engagement.

- **Site A**, a tertiary teaching hospital, demonstrated high motivation among two key neurosurgeons and a neuroanesthesiologist intensivist. However, despite their support, a key barrier was the reluctance to discharge tracheostomised patients expected to recover and be decannulated within a few weeks, potentially influencing the primary outcome.
- **Site B**, also a medical teaching institution but with a higher patient load and lower socioeconomic profile, had a cohesive neurosurgical and ICU team already practising informal family task-sharing. Their main concern related to ensuring the safety and consistency of family-led care amidst high turnover.
- **Site C**, a private tertiary hospital serving higher socioeconomic groups, had interested intensivists but limited support from the neurosurgical team, possibly due to conflicts of interest linked to ownership of private post-discharge facilities. While baseline data collection was completed, implementation was actively hindered by the neurosurgical unit and affiliated post-discharge providers, making intervention delivery unfeasible.

In view of these barriers, after four months of baseline data collection and four weeks of attempted implementation, Site C was withdrawn from the implementation. To preserve comparability across three sites and optimise use of staff and resources, the AIR intervention was reinstated at the original pilot site—AIIMS Bhubaneswar (Site D). Since the program infrastructure had been discontinued earlier, a stakeholder re-engagement meeting was held with neurosurgery, neurology, trauma, and ICU teams to reintroduce the intervention. A four-month baseline data collection period preceded reimplementation to avoid contamination as far as possible. Stakeholders were informed of the reintroduction only after baseline data collection was completed. Figure 2.

[figure not shown]

Figure 2. Project Timelines. Pre-implementation (blue) = usual care and baseline observation; Implementation (orange) = active intervention delivery; Maintenance (green) = sustained delivery under routine conditions; Diagonal hatching = non-routine phases (interrupted pilot activity or re-established implementation).Site C had 16 weeks of Pre-Implementation and 4 weeks of Implementation phases, and is not displayed here.

Note-Time is shown in study weeks (analytic time points) and is not calendar-aligned; phase transitions reflect site-specific initiation and interruption rather than fixed dates.

**Amendment to Statistical Analysis Plan**

As per the initial protocol, the analysis plan proposed conducting either an **interrupted time series (ITS)** analysis or a **pre–post design**, contingent on the achieved sample size. However, following the withdrawal of Site C, it was decided that the **primary analysis** would be a **pre–post comparison** of outcomes with Sites A and B, assessing differences before and after intervention implementation. In addition, a **secondary interrupted time series analysis** would be conducted, incorporating data from Sites A, B, and D (AIIMS Bhubaneswar) to evaluate temporal trends across these three participating centres. This modification ensured analytical rigour and retained the study's capacity to assess both immediate and longitudinal impacts of the AIR intervention.

The process evaluation was amended to align the planned methods with how implementation unfolded in practice across sites. While the initial plan assumed a uniform, time-bounded process evaluation across participating centres, early fieldwork identified inter-site variation in organisational readiness, discharge norms, and stakeholder engagement that directly influenced intervention delivery. Accordingly, the process evaluation was refined to emphasise longitudinal, observation-led inquiry across pre-implementation, implementation, and maintenance phases; to expand the use of ethnographic data and iterative analysis; and to explicitly examine contextual determinants of adoption, adaptation, and non-implementation. Analytical methods were clarified to include inductive realist-informed thematic analysis with subsequent deductive application of the CFIR framework. These amendments ensure that the process evaluation accurately captures fidelity, adaptation, and contextual constraints affecting delivery and supports valid interpretation of effectiveness outcomes

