###### 4.2 Study Rationale

The AIIMS ICU Rehabilitation pilot project has recruited more than 200 tracheostomised chronically ill patients and their family carers for home rehabilitation. It has been pilot tested and has shown good feasibility and acceptability among stakeholders. Preliminary data show that it has reduced the length of ICU and hospital stays and frequency of hospital-acquired infections.

A realist review of international studies reporting interventions aiming to implement family-led home care of chronically ill patients indicates that interventions that include components of co-designed training, supported discharge, and home visits for post-discharge follow-up facilitate implementation and reduce the length of stay and rehospitalisation among chronically ill patients, such as stroke survivors.

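### The only specified ITS adds former pilot Site D to the primary's Sites A and B, so as written it does not directly check the A+B pre-post result for secular trend.

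*Combined protocol and SAP*

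**What the plan says.** Section 11, Amendment to Statistical Analysis Plan, makes the primary a pre-post comparison "of outcomes with Sites A and B, assessing differences before and after intervention implementation". It adds a secondary ITS "incorporating data from Sites A, B, and D (AIIMS Bhubaneswar) to evaluate temporal trends across these three participating centres". It mentions no ITS restricted to A and B, no site term and no treatment of Site D's history.

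The form of the series has to be read from elsewhere. Section 2.0 (Sample size and population) takes the mean time to discharge of all eligible patients each week, at 16 points before and 16 after. Section 1.0 expects about five discharges per point, with fewer than two per centre per week. Section 5.1 expects a level change without a slope change and leaves the statistical model to be selected.

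On Site D, Section 4.2 says the pilot "has recruited more than 200 tracheostomised chronically ill patients and their family carers for home rehabilitation". Section 11 says AIR was discontinued there and later reinstated, following Site C's failure: "after four months of baseline data collection and four weeks of attempted implementation, Site C was withdrawn from the implementation". It also says "A four-month baseline data collection period preceded reimplementation to avoid contamination as far as possible", and that stakeholders heard of the reintroduction only after that baseline. The note to the timeline figure adds: "Time is shown in study weeks (analytic time points) and is not calendar-aligned".

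Section 2.0 also plans a same-week non-tracheostomised control group against history and maturation, and keeps it in the pre-post fallback. The amendment is silent on whether the A+B primary still uses it.

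**The concern.** A pre-post difference without a concurrent control absorbs any drift in discharge practice over the study. An ITS in the same sites is the natural way to see whether drift explains the result. Here the ITS is run on a different set of sites, and the added site differs in kind. Site D developed and piloted the intervention, so some of its practice may have persisted into the new baseline. It was also brought in late, so a given study week there probably falls in a different season from the same study week at A and B.

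If the primary and the ITS disagree, a reader of the planned output could not tell whether trend at A and B or the inclusion of Site D was the cause. If they agree, the agreement is partly about another site.

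**Working it through.** **1. The plan's own figure.** 16 + 16 = 32 time points; 32 × 5 = 160, which reproduces the stated figure of about 160 patients. Five per point over three centres is 5/3 = 1.67 per centre per week, consistent with fewer than two. (The Section 5.2.4 target of two per centre per week would give 3 × 2 × 32 = 192, which does not match.) So a point of five needs three centres combined. This supports reading the planned ITS as one combined series, though the plan does not say so outright.

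**2. Carry-over at Site D.** Let c be the share of the AIR effect already present in Site D's baseline (assumed; the documents give no figure). With equal site weights and a common level change, the estimate as a share of the true effect is (1 + 1 + (1 − c))/3 = 1 − c/3:

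| c | Share of true effect |
|---|---|
| 0.25 | 0.92 |
| 0.50 | 0.83 |
| 0.75 | 0.75 |

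**3. Trend in A and B.** With weeks 1–16 and 17–32 the mean weeks are 8.5 and 24.5, so an uncontrolled pre-post difference picks up 16 times the weekly trend. With a four-week implementation gap it is 20 times. Noise-free illustrations of the level-change model, with all effects and trends assumed:

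| Scenario | Pre-post A+B | ITS A+B (slope; level) | ITS A+B+D, common terms (slope; level) |
|---|---|---|---|
| A+B trend −0.2 days/week, no effect; D flat, no effect | −3.2 (−4.0 with gap) | −0.2; 0 | −0.133; 0 |
| A+B trend −0.2 days/week, no effect; D flat, effect −3 days | −3.2 (−4.0 with gap) | −0.2; 0 | −0.133; −1.0 |
| No trend; effect −4 days in A+B, −1 day in D | −4.0 | 0; −4.0 | 0; −3.0 |

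Site D enters with one-third weight: (2 × −0.2 + 0)/3 = −0.133; (0 + 0 − 3)/3 = −1.0; (−4 − 4 − 1)/3 = −3.0. In the second row the combined series shows a one-day benefit although A and B had none. A site-stratified fit of the same data recovers the A+B values exactly.

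**4. Calendar time (inference only).** Section 2.0 planned baseline in months 8–11 and post-implementation data in months 14–18. If that schedule held, Site C's four months plus four weeks end around month 12. A four-month Site D baseline begun after that would run from about month 13 to month 16, overlapping the A/B post period. No actual dates are given.

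**5. Cost of restricting to A and B.** At 1.67 per centre per week: 2 × 1.67 × 32 ≈ 107 patients (about 53 per period). At two per centre per week: 128 (64 per period). With equal site volumes, equal SD and independent weeks, the standard error ratio of A+B to A+B+D is √(3/2) = 1.22.

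**6. Calendar-month indicators in an A+B model.** If A and B start together with a four-week gap, no month contains both pre and post weeks. The post-period month indicators then add up to the level-change indicator, which is fully explained by the other terms (R² = 1.00). With a four-week stagger between the sites, site intercepts, slopes and months still explain about 0.95 to 1.00 of it, depending on where the month boundaries fall.

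**The case against.** A reader might infer that the ITS cannot check the primary at all. The documents do not support that. Sites A and B are in the ITS dataset, so a run without Site D or a fit with site terms would supply the check. The amendment does not forbid either, and it never presents the ITS as a check on the primary.

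A reader might also call Site D's baseline a treated one. That too goes beyond the text. The programme had been discontinued, a new four-month baseline was collected, and stakeholders were told afterwards. What is conceded is possible residual contamination.

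Nor is the ITS the only planned protection against secular trend, because Section 2.0 plans a same-week control group. That safeguard stands in part. The amendment does not say whether the A+B primary uses it, and Table 3 marks the row containing step-down-day status as not collected for non-tracheostomised patients, so it is unclear whether the same outcome can be computed for them.

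Finally, Site D is outside the primary, so carry-over touches only a secondary estimate, and lining up sites on their own interruption is ordinary practice with staggered starts. Both are fair. They limit the seriousness of the point but do not supply the missing A+B trend analysis.

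**Conclusion.** The point holds in a limited form. Followed as written, the secondary ITS is not a like-for-like examination of the A+B pre-post result, and it brings in a previously exposed site without saying how that is handled. The dilution of a common level change is moderate: 92% to 75% of the true effect for assumed carry-over of 25% to 75% and equal site weights. Section 11 says Site B has a higher patient load, so equal weights are only a convenience. The different calendar period at Site D is an inference, and the single combined series is the natural reading rather than an explicit statement. This is a worthwhile, low-cost improvement to a secondary analysis. It does not show that the primary is biased.

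**What to change.** Pre-specify the following in the analysis plan:

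- An ITS in Sites A and B on patient-level data, with site-specific intercepts and baseline slopes and a common level change.
- Site D as a separate, site-specific estimate.
- The A+B+D ITS, with site terms, as a sensitivity analysis labelled as including a previously exposed site.
- A statement of whether the non-tracheostomised control arm enters the A+B primary and, if so, on which outcome.

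Leave calendar-month indicators out of the A+B model, since they can be collinear with the level change.

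The cost is some analysis-plan wording and a little more modelling. The A+B level change would have a standard error about 22% larger than A+B+D with equal site volumes, on about 107 to 128 patients. The planned A+B+D analysis is kept, so no information is lost.
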